#### Quality of life

The *Functional Assessment of Cancer Therapy (FACT-G, version 4)* is a brief self-report measure of general cancer quality of life for patients with any tumor type receiving cancer treatment [41, 42] The 27 items assess physical well-being, social/family well-being, emotional well-being, functional well-being, and additional concerns during the past 7 days. Items are rated on a 5-point Likert scale (0=“Not at all” to 4 = “Very much”). The FACT-G demonstrates ease of administration, brevity, reliability, validity, and sensitivity to change [42].

##### Parent-adolescent relational outcomes (mediators)

ᅟ

#### Attachment

The *Security Scale* is a 15-item measure that assesses children’s perceptions of attachment during middle childhood and adolescence [43]. This scale provides a continuous measure of security, evaluating a child’s belief in the responsiveness and availability of the attachment figure, the child’s use of the attachment figure as a safe haven, and the child’s report of open communication with the attachment figure. The Security Scale presents children with descriptions of two types of children and asks which type of child they are most like. Items are scored from 1 to 4, with greater attachment security represented by a higher score. Scores on the Security Scale have adequate internal consistency and evidence of validity based on security scores correlated with self-esteem, peer acceptance, behavioral conduct, physical appearance, and scholastic competence [44].

#### Parent-child relationship

The *Interaction Behavior Questionnaire (IBQ)* is a valid and reliable measure that evaluates agreement and conflict in parent-child dyads [45]. The original IBQ was adapted into a short form consisting of 20 true/false items assessing communication-conflict behavior. Higher scores indicate a more positive relationship.

#### General communication

In this research, 10 questions will be asked to measure general communication between a parent and his/her adolescent child [46]. Each question is scored on a 4-point Likert scale ranging from 1 (strongly disagree) to 4 (strongly agree). It is a valid and reliable measure; higher scores indicate better communication.

#### Potential treatment moderators

At baseline, parents will provide information about their adolescent child’s age and gender. They will also be asked to report household income, education, and family size, age, gender, marital status, cancer diagnosis and stage, time since diagnosis, treatment modalities and frequencies, and mental health diagnoses and treatment.

#### Parental stress

The 15-item (Likert scale) *Parenting Concerns Questionnaire (PCQ)* has good internal consistency (α = .83) and is a valid measure of parenting distress among cancer patients [47]. There are 3 subscales and a total scale, with higher scores indicating more parental stress: (1) practical impact of illness on child; (2) emotional impact of illness on child; (3) concerns about co-parent. PCQ scores are significantly associated (*P* < .01) with standardized measures of psychosocial distress (Distress Thermometer, Hospital and Anxiety Depression Scale, and FACT-G) in the expected directions.

#### Perceived level of group support

The *Helpful Group Experiences (HGE)* is a 17-item adapted valid and reliable measure that assesses the helpfulness of experiences in a support group [48, 49]. The HGE includes 5, four point-subscales, including altruism (e.g., “I offered empathy or compassion”), cognitive growth, and informational (e.g., gained access to important information) support (e.g., got support and encouragement). The HGE will be used only at post-intervention (week 8) to assess parents’ perceptions of group experiences. The 5 subscales have acceptable internal consistency ranging from α = .71–.93 [49].

### Satisfaction with intervention

#### Consumer satisfaction

Parent and Adolescent Consumer Satisfaction includes several Likert and open-ended questions to assess satisfaction with an intervention program, skills taught, teaching methods, and group facilitators [50]. This tool will be used only at post-intervention (week 8) and has been used successfully in parenting intervention research and in two previous pilot studies [8, 27, 28].

### Analysis plan

#### Primary aim 1

Compare the efficacy of FFCT to PED in reducing child depressive symptoms (CDI) in AA adolescents at post-treatment using an intention-to-treat (ITT) analysis. ANCOVA is the most powerful test of the primary study hypothesis and will be estimated by an equation such as:$$ CDI{(Post)}_i={\beta}_0+{\beta}_1\times CDI{(Pre)}_i+{\beta}_2\times FFC{T}_i+{\sum}_{\mathrm{j}=1}^{\mathrm{J}}{\beta}_j Co{v}_{ji}+{\epsilon}_i $$

Evidence in favor of the study hypothesis will be indicated by a significant negative coefficient for β_2_. In addition to the main effects shown here, we will evaluate the assumption of parallel slopes by a baseline×FFCT interaction. We will evaluate sensitivity of study conclusions to missing data using a range of suitable ITT methods (e.g., last observation carried forward, direct maximum likelihood, multiple imputations). Methods for non-ignorable nonresponse (pattern mixture models) will also be evaluated as indicated. Significant treatment differences at posttest will be followed by subsample analyses to determine individual characteristics associated with differences in treatment effects (e.g., heterogeneity). Standard errors will adjust for clustering within site and family via the cluster-adjusted sandwich estimator.

#### Secondary aim 2

Compare the efficacy of FFCT to PED in reducing parental stress (PCQ) in AA parents at post-treatment using ITT analysis. We will evaluate the secondary aim for posttest differences in parental stress (PCQ) in a fashion parallel to that used for the Aim 1, using an equation such as:$$ PCQ{(Post)}_i={\beta}_0+{\beta}_1\times PCQ{(Pre)}_i+{\beta}_2\times FFC{T}_i+{\sum}_{\mathrm{j}=1}^{\mathrm{J}}{\beta}_j Co{v}_{ji}+{\epsilon}_i $$

Evidence in favor of the study hypothesis will be indicated by a significant negative coefficient for β_2_.

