**Methods:**

A sample of 172 African American families will be enrolled from two diverse oncology centers (Helen Graham Cancer Center in Newark, DE, and Kimmel Cancer Center in Philadelphia, PA). Eligible families will be randomized either to a 5-session intervention Families Fighting Cancer Together (FFCT) or a 5-session parent-only psycho-educational (PED) program. Assessments will occur at weeks 0 (baseline), 8 (end-of-treatment), 24, and 52.

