### Statistical power

Sample size was determined from pilot study data for the primary outcome (child depressive symptoms on the CDI) and endpoint (post-treatment) using power = 8 and α = .05 [27]. For all other analyses, minimum detectable effects are presented for fixed sample size. Pilot data indicate a greater decrease in depressive symptoms from pre-treatment to post-treatment among children in the FFCT intervention compared with children receiving PED equivalent to an effect size of Cohen’s d = 0.38, and pre-post correlations of 0.68. This suggests that a sample size of 60 families per study arm will yield power ≥ .8 with α = .05. Conservatively assuming retention of 70% (retention in the single site pilot was 85%), this indicates that recruitment of 172 study participants will ensure adequate statistical power for testing the primary study aim.

For tests of differences at post-treatment, a total sample size of 120 is used. Minimum detectable effects (in SD units) vary as a function of the correlation between pre-treatment and post-treatment measures and range between 0.31 for a correlation of 0.8 and 0.51 for a correlation of 0.2. Test of differences at 12-month follow-up assume that 80% of participants at post-treatment are retained to follow-up but benefit statistically from two additional occasions of measurement. Minimum detectable effects (in SD units) vary as a function of the correlation between pre-treatment and follow-up measures and range between 0.28 for a correlation of 0.8 and 0.38 for a correlation of 0.2.

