### Randomization

Randomized permuted blocks will be used to allocate groups of parent-adolescent dyads to each study arm (FFCT or PED). The data manager will prepare complete sets of allocations which will be placed in sequentially numbered sealed opaque envelopes containing treatment assignments for each group of 5 to 8 families. Once 5 families are recruited, group allocation will be made after a week has elapsed without any additional family participants recruited or once 8 families have been recruited, whichever occurs first.

The assessment team will be blind to the allocation condition and know only the serial numbers. At randomization, following baseline assessments, only the program manager opens the envelope for the group’s allocation. This approach provides both dynamic balancing and prospective partial blinding of the project manager to treatment assignment. At the end of the study, unused sealed envelopes will be retained along with the log to assure that randomization has been carried out as assigned.

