#### Treatment Fidelity

Standardized fidelity treatment checklists were developed for FFCT and PED to monitor treatment integrity and dosage. These treatment checklists were tested in our previous pilot studies [22, 27]. Monitoring involves both dosage and purity; dosage of the intervention is measured by the completion of the number of sessions. Purity involves monitoring the extent to which the program was delivered as designed. All sessions will be video-recorded. Once the trial begins, the clinical supervisor will meet separately with the two teams of therapists weekly to review their video-recorded sessions, complete the fidelity checklist for both FFCT and PED sessions, and re-train as necessary to monitor treatment fidelity. Second, a random sample of 25% of all group sessions will later be rated by 2 coders blind to treatment assignment on the same checklist in years 4 and 5. With a total of 172 families (86 families/arm) who attend 5 (90-min to 2-h) support group sessions, it is estimated there will be 14 FFCT groups with 5 to 8 families/group and 14 PED groups with 5 to 8 families/group run during the course of this study. All intervention sessions will be video recorded using a HIPAA-compliant video system at and stored in an encrypted secure server; 50% of cases (*n* = 7 groups of PED and 7 groups of FFCT) will be reviewed after each session using a fidelity checklist. To minimize drift, the PI and project manager will review a random sample of 25% of FFCT cases (*n* = 4 groups) and 25% of PED cases (n = 4 groups) for each therapy team (2 therapists/team) to provide ongoing feedback. The clinical supervisor, PI, and project manager will view the video-recorded sessions and use the fidelity treatment checklists to monitor treatment integrity and dosage. After the PI and project manager review sessions each week, they will share feedback immediately with the clinical supervisor and 3 therapists and at monthly meetings with the intervention team to direct restraining efforts as needed.

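### The plan randomises groups of 5 to 8 families, but the standard errors for Aims 1 and 2 are clustered on site and family only, leaving out the randomised group

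*Protocol article*

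**What the plan says.** **Allocation.** The Randomization section states: "Randomized permuted blocks will be used to allocate groups of parent-adolescent dyads to each study arm". The allocations are held in "sequentially numbered sealed opaque envelopes containing treatment assignments for each group of 5 to 8 families". The group is assembled before it is allocated: "Once 5 families are recruited, group allocation will be made after a week has elapsed without any additional family participants recruited", or when the eighth family joins, if that is sooner.

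**Number of groups.** Under Treatment Fidelity, "it is estimated there will be 14 FFCT groups with 5 to 8 families/group and 14 PED groups with 5 to 8 families/group". That makes about 28 randomised units.

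**Delivery.** The section on the treatment models has FFCT adolescents meeting as a group in sessions 1 and 2, parents in session 3, and several families together in sessions 4 and 5. In PED only the parents attend, also as a group.

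**Analysis.** Primary aim 1 is an ANCOVA with one residual per participant and no group term. Its standard errors are covered by one sentence: "Standard errors will adjust for clustering within site and family via the cluster-adjusted sandwich estimator". Secondary aim 2 uses the same form of model. In Exploratory aim 3a the subscript k denotes differences between the treatment arms, so it is not a term for the randomised group either.

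**Sites.** The abstract states: "A sample of 172 African American families will be enrolled from two diverse oncology centers". The recruitment section adds community recruitment sites without saying how many.

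**The concern.** When a group is allocated as one unit, the group is the independent unit for comparing the arms. Any correlation between families in a group adds to the variance of the treatment coefficient. It can come from shared sessions, shared facilitators or being recruited at the same time. The standard error has to be built at group level or above to include it.

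Of the two levels named, family is finer than the group and cannot pick up variation between groups. Site is coarser and could do so in principle, but only with enough sites. At stake are the p-value and confidence interval of the only primary test, and those of the secondary test that copies it. The power calculation rests on the same assumption that families are independent.

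**Working it through.** **Inputs.**
- From Statistical power: "equivalent to an effect size of Cohen’s d = 0.38, and pre-post correlations of 0.68"; α = 0.05; 60 families analysed per arm; 70% retention; 172 enrolled.
- From Treatment Fidelity: 28 groups. This gives 172/28 = 6.1 families enrolled and m = 120/28 = 4.3 analysed per group.
- Assumed: the ICC, which the document does not give. The range is 0.02 to 0.15 on the baseline-adjusted residual scale.

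**1. The plan's own figure.** The residual SD is √(1 − 0.68²) = 0.733. Families per arm = 2 × 0.733² × (1.960 + 0.842)² / 0.38² = 58.4, so 59 by the normal approximation and 60 by the t distribution. Power at 60 per arm is 0.81 (normal) or 0.80 (t). Enrolment is 120/0.70 = 171.4, so 172. The plan's figures reproduce, but only with a design effect of 1.

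**2. Effect of leaving out the group.** Design effect DE = 1 + (m − 1) × ICC. If the standard error ignores DE, the true two-sided type I error is 2 × [1 − Φ(1.96/√DE)]. Power with the group respected uses the noncentrality 0.38 / (0.733 × √(2 × DE/60)) and t on 28 − 2 = 26 df.

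| Residual ICC | DE | Type I error, group ignored | Power, t(26) |
|---|---|---|---|
| 0 | 1.00 | 5.0% | 0.78 |
| 0.02 | 1.07 | 5.8% | 0.75 |
| 0.05 | 1.16 | 6.9% | 0.72 |
| 0.10 | 1.33 | 8.9% | 0.66 |
| 0.15 | 1.49 | 10.9% | 0.61 |

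The first row shows that a small part of the power loss comes from the 26 df alone.

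**3. Simulation of the ANCOVA** (28 groups, 3 to 6 analysed families each, r = 0.68, no treatment effect, nominal 5%).
- Family-level sandwich, correlation in both arms: about 6, 7, 9 and 12% at ICC 0.02, 0.05, 0.10 and 0.15.
- Family-level sandwich, correlation in FFCT only: about 5% at 0.02, 5 to 6% at 0.05, 7 to 8% at 0.10, and 8 to 9% at 0.15.
- Group-level sandwich with t(26): about 5 to 6% throughout.

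**4. The site level.** The model has an intercept, so the score contributions sum to zero. With two sites the two sums are equal and opposite, and the variance estimate has rank 1. If families are nested in sites, two-way clustering gives V(site) + V(family) − V(site∩family). The last two terms cancel, leaving V(site). Simulated with two sites and an assumed 70/30 split, this gives about 33% false positives against a normal or residual-df reference, at every ICC including 0. Against t on 1 df the type I error is about 5 to 6%, but power for d = 0.38 drops to about 0.2.

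**The case against.** **The ICC is unknown and may be small.** This stands. Groups are formed by order of recruitment and not from existing communities. At an ICC of 0.02 the type I error is about 6%. A reader might infer that the primary p-value is simply wrong; the document supports only that it is wrong to the extent that outcomes correlate within groups.

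**PED adolescents never meet as a group.** This also stands. The primary outcome is the adolescent's CDI, so direct correlation is plausible mainly in FFCT. That lowers the inflation without removing it. In the other direction, if the ICC is defined on the unadjusted outcome, the same nominal value gives more inflation: about 10% at 0.05 and 13% at 0.10 with both arms correlated.

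**Site clustering would absorb group correlation.** It could with many sites and groups formed within sites. The document says neither. A reader might equally infer a false-positive rate of one in three. That figure needs exactly two sites, clustering at site level, and a normal or residual-df reference. The number of community recruitment sites is not given and no reference distribution is stated, so it is one reading of the sentence. It and the family-level inflation are alternative readings and do not add up.

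**The bootstraps in Aims 3b and 3c.** A reader might extend the fault to these. The plan states no resampling unit for them, so the document does not support that claim.

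**An unseen analysis plan could settle it.** This does not answer the point. The article does not leave the clustering levels open; it names them, and they do not match its own randomisation.

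**Conclusion.** The point holds for Aims 1 and 2: the stated clustering levels leave out the unit that is randomised. If standard errors are taken at family level, the type I error is about 6 to 12% over residual ICCs of 0.02 to 0.15 with both arms correlated, and about 5 to 9% if only FFCT is. These figures assume 28 groups with about 4 analysed families each and r = 0.68. If standard errors are taken at site level with only two sites, the test is either far too liberal or has little power, depending on the reference distribution. Neither reading gives a dependable primary test, and the correction is cheap, so it should be made before analysis. The power of at least 0.8 assumes independent families. With 26 df it is about 0.75, 0.72 and 0.66 at ICC 0.02, 0.05 and 0.10.

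**What to change.** For Aims 1 and 2, replace the sentence on standard errors so that the randomised group is the clustering level, and choose one of two methods in advance:
- a random intercept for group with Kenward-Roger degrees of freedom; or
- group-clustered standard errors with the CR2 correction and Satterthwaite degrees of freedom.

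The degrees of freedom will be roughly the number of groups minus 2, so about 26. They should follow from the data and not be fixed at 26, because the 14 groups per arm are an estimate. Keep family as a level nested in group where siblings are enrolled. Enter site as a fixed covariate and not as a cluster level. Add the group level to the Aim 3a model.

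Restate the power under an assumed ICC with its range. As a guide, 60 × DE gives 64, 70 and 80 analysed families per arm at ICC 0.02, 0.05 and 0.10. At 70% retention that is about 183, 200 and 229 enrolled, against 172.

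**Cost.** The analysis change is wording only, since group membership is recorded through the allocation. The interval becomes somewhat wider. The restated power may fall below 0.8, and the sponsor would then have to accept that or enrol more families.

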FFCT includes the following 5 sessions: Sessions 1 and 2 are 90-min adolescent support group sessions (up to 8 AA youth). Session 1 focuses on improving awareness and understanding about how their parents’ cancer is affecting them. The group facilitators focus on the promotion of empathy and understanding among group members, reducing tension, increasing fun activities, and maintaining normal routines. In session 2, the facilitators help adolescents develop adaptive coping skills and prepare youth to more openly communicate their thoughts, fears, and feelings to their parents about the cancer experience during sessions 4 and 5. Session 3 is a 2-h, parent-only support group session to help parents get ready to talk more openly to their adolescents during sessions 4 and 5. This session focuses on: (1) therapist alliance and trust building with parent(s); (2) improving parents’ self-care while navigating cancer; (3) teaching parents to listen and to validate their adolescent’s experiences so youth can more openly communicate fears and worries; and 4) promoting more open communication between parents and children using Afro-centric resilience. Sessions 4 and 5 includes two (2 h) interactive multiple family group sessions (up to 8 families). In session 4, group facilitators focus discussions on parental cancer and on the stress it places on families, in particular helping adolescents openly share their thoughts, feelings, and fears with parents and helping their parents to listen and validate them. Session 5 focuses on facilitating secure parent-child attachment, so adolescents can talk directly to their parents and parents can respond to their children’s worries/fears in a responsive and empathic way. Facilitators focus discussions during sessions 1 to 5 on faith, spirituality, resilience, and utilizing fictive kin and the African American community (e.g., the church) for practical, emotional, and spiritual support [30].

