Psychoeducation (PED) consists of only parents receiving a 5-session (1 session every 2 weeks over 8 weeks) psycho-education group, which was adapted from an American Cancer Society (ACS) free online educational program [31]. This program, (previously known as *I Can Cope*) was developed for cancer patients, families, and friends. This standardized online program included self-paced lectures about cancer: managing treatments and side effects; eating healthily during and after treatment; and finding resources. Explicit permission was attained from ACS to use this program. The purpose for choosing this program as the PED comparison group was it closely resembled what oncology clinics offer to adult cancer patients [32]. The ACS’s structured PowerPoint lectures and videos from *I Can Cope* have recently been updated and organized differently. Group facilitators will cover the following in 5 (1-h) psycho-education sessions with the most current ACS informational materials: (1) managing effects of illness/treatment; (2) nutrition during treatment; (3) mobilizing resources/support; (4) addressing self-esteem/intimacy; and (5) integrating mind, body, and spirit. This comparison group controls for contact time with group facilitators, filling out baseline information, posttest, 6- and 12-month follow-up assessments; it also restricts the focus on parent-child communication and attachment in the experimental group (FFCT).

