#### Exploratory aim 3a

Determine trajectories of child depressive symptoms (CDI), anxiety (RCMAS), and parental stress (PCQ) from baseline to 12-month follow-up. Aim 3a will initially be evaluated using random coefficients models using equations such as:$$ CD{I}_{ij k}=\left({\beta}_0+{\beta}_{0i}+{\beta}_{0k}\right)+\left({\beta}_1+{\beta}_{1i}+{\beta}_{1k}\right)\times Tim{e}_{ij}+{\sum}_{\mathrm{j}=1}^{\mathrm{J}}{\beta}_j Co{v}_{ji}+{\epsilon}_i $$where coefficients without subscripts represent fixed effects, coefficients indexed by i represent individual-level random effects, subscripts indexed by j represent time effects, and subscripts indexed by k represent treatment group differences. Evidence in favor of our hypothesis would be indicated by a significant negative coefficient for β_1k_ for CDI, RCMAS, and PCQ.

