#### Exploratory aim 3c

Determine whether pre-post changes in parent-adolescent attachment and communication mediate the association between treatment and adolescent depressive symptoms (CDI) and anxiety (RCMAS) at 6- and 12-month follow-ups. Consistent with current recommended practice, potential mediators will be estimated using structural equation modeling with standard errors estimated using a large (e.g., 5000) number of replicate bootstrap samples. Variance will be partitioned into direct, indirect, and total effects for interpretation. Evidence for mediation is indicated by significant indirect effects. In addition to significance testing, we will evaluate these exploratory aims from an accuracy in parameter estimation (AIPE) framework to bracket estimated effect sizes using half-widths.

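### The primary analysis adjusts for clustering by site and family but not by therapy group, the unit randomised and treated, so its test is anti-conservative if outcomes correlate within groups

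*Protocol article*

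**What the plan says.** On allocation, the Randomization section states: "Randomized permuted blocks will be used to allocate groups of parent-adolescent dyads to each study arm". It describes "sequentially numbered sealed opaque envelopes containing treatment assignments for each group of 5 to 8 families", so one draw fixes the arm of every family in a group.

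On delivery, FFCT consists of adolescent group, parent group and multiple-family group sessions. PED is a parent group. The Treatment Fidelity section expects 172 families, 86 per arm, in 14 FFCT and 14 PED groups.

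On analysis, Primary aim 1 is an ANCOVA of post-treatment CDI on baseline CDI, arm and covariates. Its only statement on clustering is "Standard errors will adjust for clustering within site and family via the cluster-adjusted sandwich estimator". Aim 2 (PCQ) is to be analysed in parallel. For Aim 3a, "coefficients indexed by i represent individual-level random effects", and the index k denotes treatment group differences, meaning the arms. No therapy-group term appears in any model.

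**The concern.** When groups are randomised, the standard error of the treatment effect has to reflect variation between groups. Families in one group share sessions, each other's company and a recruitment window. FFCT is built to work through group members, and Aim 3b predicts larger effects where parents perceive more group support. Some positive correlation is therefore plausible, at least among FFCT adolescents and among parents in both arms.

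Neither named level deals with this:

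- **Family** is nested within the group. Clustering on it cannot capture correlation between different families in a group. Where a family supplies one adolescent, as the dyad wording suggests, it leaves the standard error almost unadjusted.
- **Site** would contain the groups if groups are nested in sites, which is not stated. The abstract names two centers, and a sandwich estimator built on two clusters is unreliable.

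What is at stake is the primary efficacy claim. The error runs toward declaring FFCT effective when it is not.

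**Working it through.** **Inputs from the protocol.** d = 0.38, pre-post correlation 0.68, α = 0.05 (taken as two-sided), 60 families per arm analysed, 70% retention (Statistical power); 14 groups per arm, 86 families per arm (Treatment Fidelity); groups of 5 to 8 (Randomization). **Assumed:** a covariate-adjusted group ICC of 0.01 to 0.10, because none is given.

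**1. The plan's own figure.** The residual SD after ANCOVA is √(1 − 0.68²) = 0.733. Two-sided 5% and 80% power give 59 per arm by normal approximation. With the noncentral t, power is 0.797 at 59 and 0.804 at 60, so 60 per arm reproduces. Then 120/0.70 = 171.4, or 172 enrolled. Both figures reproduce with independent families and no design effect.

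**2. Families per group.** At analysis m = 60/14 = 4.3; with full retention m = 86/14 = 6.1.

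**3. Type I error if the group is ignored in both arms.** The design effect is DE = 1 + (m − 1) × ICC, and the actual error is 2 × [1 − Φ(1.96/√DE)].

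| ICC | DE (m = 4.3) | Type I error, m = 4.3 | Type I error, m = 6.1 |
|---|---|---|---|
| 0.01 | 1.03 | 5.4% | 5.6% |
| 0.02 | 1.07 | 5.8% | 6.2% |
| 0.05 | 1.16 | 6.9% | 8.1% |
| 0.10 | 1.33 | 8.9% | 11.1% |

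**4. Simulation of the ANCOVA.** The set-up was 28 groups of 5 to 8 families, 70% retained, no treatment effect, 6,000 trials per ICC.

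| ICC | Family-level SE | Group-level sandwich, t with 26 df |
|---|---|---|
| 0 | 5.1% | 5.5% |
| 0.02 | 6.1% | 5.8% |
| 0.05 | 6.9% | 5.4% |
| 0.10 | 9.7% | 5.7% |

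**5. Correlation among FFCT adolescents only.** A separate simulation of the same layout, without the baseline covariate, gave 5.6%, 6.3% and 7.6% at ICC 0.02, 0.05 and 0.10. As a rough check with equal group sizes, the variance inflation is the mean of the two arms' design effects. At ICC 0.05 that is (1.164 + 1)/2 = 1.082, and 2 × [1 − Φ(1.96/1.040)] = 6.0%. Unequal group sizes push the simulated value somewhat higher.

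**6. Site as the cluster.** With groups nested in two sites, the site-level sandwich rejected in about 33% of null trials against a normal reference. Against t with 1 df it rejected in 5.6 to 6.2%, but the critical value is then 12.7, which leaves no useful power.

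**7. Cost of the correct level at ICC 0.05.** Interval width: √1.164 × (2.056/1.980) = 1.079 × 1.038 = 1.12. Power: the noncentrality without clustering is 0.38/(0.733 × √(2/60)) = 2.84. Dividing by 1.079 gives 2.63, which with 26 df yields power 0.72.

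**The case against.** **The inflation is conditional.** The protocol gives no ICC. At zero there is no inflation, and at 0.01 it is slight. This stands. A reader might infer that the test certainly exceeds 5%, or does so by a wide margin. The documents do not support that: 9% or more needs an ICC near 0.10 in both arms, or larger groups.

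**PED adolescents never meet.** PED is parent-only, so for adolescent CDI the lower FFCT-only figures may be closer to the truth. This stands for Aim 1, although a shared recruitment window could add some correlation in PED. In Aim 2 parents meet in both arms.

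**Facilitators are largely common to all groups in an arm.** Each therapist team serves many groups, so shared facilitators add little to variation between groups within an arm. This stands. The case rests on shared sessions, peers and recruitment period.

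**Site is named as well as family.** The 5.4 to 10% figures describe a family-level reading. A reader might instead take the 33% from site-level clustering as the plan's error rate. That does not follow, because the protocol states neither that groups are nested in sites nor which reference distribution applies. Community recruitment sites are also mentioned, without a number. The result shows only that two clusters cannot stand in for the group.

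**Detail may sit elsewhere.** For Aims 3b and 3c this is right. The plan says only "with standard errors estimated using a large (e.g., 5000) number of replicate bootstrap samples", and how the bootstrap resamples is something an article may leave to the full analysis plan. A reader might count the silence as a further error, but it is not one. The Aim 1 sentence differs because it positively fixes the cluster levels and omits the one that the randomisation requires.

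**Conclusion.** The clustering statement for Aim 1 is wrong as written and contradicts the protocol's own unit of randomisation. Aim 2 inherits the fault by being analysed in parallel. The direction is certain for any positive group ICC under family-level standard errors. The size is not certain, since the ICC range is an assumption: roughly 5.4% to 10% for ICC 0.01 to 0.10 in both arms with about 4.3 analysed families per group, and lower for CDI if only FFCT adolescents are correlated. Even a modest inflation matters here, because it affects the primary test, favours a false claim of efficacy, and can be removed by rewording the analysis. It should be corrected before outcome data are analysed. The Aim 3a equation is offered as an example, so there the missing group term calls for a consistent amendment and is not a separate finding.

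**What to change.** In the Analysis plan, make the randomised therapy group the cluster level for Aims 1 and 2. Two suitable forms are:

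- a group random effect with Kenward-Roger or Satterthwaite degrees of freedom, about 28 − 2 = 26; or
- a bias-corrected sandwich estimator clustered on group, with a t reference on about 26 degrees of freedom.

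Allow the group variance to differ by arm, since adolescents meet only in FFCT. Keep the site adjustment as a fixed covariate. Keep family nested within group where a family supplies more than one adolescent. Carry the group effect into the Aim 3a model.

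No new data should be needed, because allocation is made and logged by group. The cost is precision. At an assumed ICC of 0.05, intervals are about 12% wider and power at 60 per arm is about 0.72, so the stated power of at least 0.8 should be restated with its ICC assumption. Counting the design effect alone, enrolment for the planned power would be about 2 × 70/0.70 = 200 families (60 × 1.164 = 69.9, rounded up to 70 per arm) instead of 172.
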